### Trial design

This intervention trial has a randomized, controlled, multicentre, and single-blinded design with 3 parallel groups, a 1:1:1 allocation ratio, and 4 measurement times: pre-intervention, immediately after the intervention, and two follow-ups (at 6 and 12 months; see Fig. 1).

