#### Treatment as usual (TAU)

Participants in this group will be provided with common primary care treatment by a GP in a face-to-face consultation that seldom lasts more than 10 min. TAU usually consists of pharmacological treatment, though it might also involve practical advice or even no treatment at all [51]. The first consultation will count as part of the recruitment process and, if the patient agrees to participate in the trial, no therapy will be provided until they are allocated to a group. Once in the TAU intervention, if the practitioner recommends psychological treatment (e.g., referral to specialized care), the participant would be excluded to avoid contamination between clusters. TAU does not comprise a specific number of sessions; it will end when the GP considers the patient recovered.

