### Blinding

The trial will be single-blinded. Assessors and data managers will be blinded insofar as they will have no knowledge of the treatment allocation and will not be involved in the interventions. However, even though participants will be blinded during the pre-treatment evaluation, they will probably not remain blinded once allocated, since the experimental conditions are qualitatively different. For the same reason, the clinical psychologists who perform the transdiagnostic treatments will not be blinded. Since participants might consult their GPs during the intervention period, they will be asked not to share information concerning their allocation; this will ensure that the GPs are blinded.

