#### Collection process

First, the 4-item PHQ ultra-brief subscale (PHQ-4) [91] will be used for the recruitment phase. The PHQ-4 gathers 2 items from the PHQ-2 and 2 from the GAD-2 (short versions of the PHQ-9 and GAD-7, respectively). It has been used in a Spanish primary care population (Spearman-Brown’s *ρ*_PHQ-4_ = .72; *ρ*_PHQ-2_ = .86; *ρ*_GAD-2_ = .76) [92]. A score greater than or equal to 3 would indicate the need for additional assessment (PHQ-2: a sensitivity of 90% and a specificity of 61%; GAD-2: a sensitivity of 88% and a specificity of 61%). It can be an extremely useful tool, as it helps to accelerate the screening process. It has been suggested, however, that both PHQ-2 and GAD-2 sum scores should be regarded separately in primary care samples [92]. The first item from the PHQ-PD has been added to screen panic disorder.

Second, depression, anxiety, panic, and somatizations will be assessed through the PHQ subscales mentioned above. If a participant scores as having a severe ED (depressive or anxiety disorder) or a non-emotional mental illness, or if the diagnosis is not clear, they will undergo a second evaluation with a gold-standard tool. The Structured Clinical Interview for DSM Axis-I Disorders (SCID-I) [93] will be used to assess panic and depression disorders and the Composite International Diagnostic Interview (CIDI) [94] will be used for GAD (since the former may not be adequate as it only includes one item for GAD). If these tools confirm the PHQ results, the patient will be referred to their GP, who will refer them to specialized care. The same will apply to those who score high in the SDS. All measures, except the PHQ-4, the SCID-I, the CIDI, and the treatment satisfaction question, will be collected at baseline, immediately after treatment, and 6 and 12 months later (see Table 2). Data will be also collected from medical records for the 3 months before participation in the study. To facilitate completion, the questionnaires may be answered in person, by email, online, or by phone.

To reduce the number of withdrawals, the clinical psychologists will telephone the participants to encourage them to continue with the treatment and/or to participate in the follow-up assessments. People who drop out of the intervention will still be invited to complete the questionnaires, especially at the first post-treatment assessment (immediately after the intervention).

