#### Cost analysis

Cost-related data will be collected through medical records and ad hoc questionnaires, from 3 months before inclusion in the study to 12 months after the intervention. Direct costs will be calculated by adding the ED-related costs due to medication use (antidepressants, anxiolytics, hypnotics, and sedatives), medical tests and other health services, and health personnel (primary/specialized care and public/private care). Medication costs will be calculated by multiplying price per milligram (€/mg) according to the Vademecum International (including VAT) [96] by the daily dose (mg) and the number of days of drug treatment. Cost data relating to medical tests and the use of health services will be obtained through the fee information published on the Andalusian Health Service’s official website [97]. Since a group psychotherapy session does not have a specific tariff, it will be considered as a GP consultation without medical tests because GPs and clinical psychologists have similar basic salaries [98]. Indirect costs will be calculated by multiplying the days of ED-related sick leave by the participant’s current daily minimum salary; the expense of replacement workers will also be factored in when incurred. Total costs will be obtained by summing direct and indirect costs.

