### Anticipated limitations

We recognize that our protocol has several limitations, and we expect difficulties in its execution. First, the trial design excludes some groups to minimize confusion variables (minors, older people, and patients with severe mental disorders and/or with intellectual, legal, or high functional disability), so additional research will have to be carried out on these populations; and the single-blind approach will not allow us to control patients’ therapy expectations, though participant blinding is ordinarily not feasible in RCTs that compare psychotherapies.

Second, we might encounter obstacles during recruitment. In the first phase, the great care saturation faced by GPs (i.e., they have to deal with great numbers of patients in a short time) might make enrolment difficult; moreover, since there has never been a psychotherapy culture in primary care, some of them might have little motivation to collaborate. In the second phase, the main limitation might be the measurement tools. Brief instruments have been included in the protocol because primary care requires rapid assessment; however, they do not have the same diagnostic accuracy as gold-standard tools such as the SCID. Furthermore, because these questionnaires are self-administered, completion and the veracity of answers are less controlled than clinical interviews. Nonetheless, the tools included have been validated and tested in Spanish primary care, and they accelerate the diagnostic process in clinical practice.

Third, the interventions might have limitations. For example, each treatment may have a different duration, especially TAU, so this might impact effectiveness (though we will consider this in our analyses). Also, each intervention will be carried by different personnel (i.e., GPs and clinical psychologists), so this might affect the results. In addition, TAU might generate expectations in participants, and they cannot be feasibly blinded. An alternative may be sham therapy, but TAU is closer to clinical reality, so it provides better external validity. The level of adherence to the protocol is another difficulty envisaged, though the therapists will be supervised by PhD trainers during the treatment period.

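### All post-baseline assessments and the cost window are timed from the end of treatment, but TAU ends only at GP-judged recovery, so TAU has outcome-dependent visit dates and a different horizon

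*Protocol article*

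**What the plan says.** - **Assessments.** Under Collection process, the measures "will be collected at baseline, immediately after treatment, and 6 and 12 months later". Trial design gives the same four occasions for all three arms, and Hypothesis 5 counts the two follow-ups from the intervention, not from randomisation.
- **Costs and QALYs.** Under Cost analysis, data are gathered "from 3 months before inclusion in the study to 12 months after the intervention". The section on cost-effectiveness and cost-utility also describes follow-up as ending 12 months post-intervention, and on that ground applies no discounting.
- **Length of treatment.** Group tCBT is seven sessions over 12–16 weeks. Individual tCBT is 6–8 sessions, with no number of weeks given. For TAU, "TAU does not comprise a specific number of sessions; it will end when the GP considers the patient recovered". TAU usually means medication, "though it might also involve practical advice or even no treatment at all".
- **Success criterion.** Statistical methods rests therapeutic success on post-intervention means and effect sizes against the controls.
- **Acknowledgement.** Anticipated limitations concedes that "each treatment may have a different duration, especially TAU, so this might impact effectiveness" and says the analyses will take this into account. Its closing lines, on patients' availability, promise an effort to keep timings alike between groups. Neither statement gives a time point, window or cap.

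**The concern.** The end of treatment is a workable anchor when the programme has a bounded length. In TAU the anchor is a judgement about the very construct the trial measures. A TAU patient who improves early is seen early and in a good state. One who improves late is seen late. One who never improves reaches no anchor at all. Where TAU amounts to no treatment, it is unclear what its end would be.

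Two things are at stake. First, the post-intervention contrast behind Hypothesis 2 and the success criterion compares tCBT at a roughly fixed time with TAU at a time linked to its own outcome. Second, the ICERs and ICURs behind Hypotheses 3 and 4 divide differences in costs and effects accumulated over windows of different length, and Hypothesis 5 carries the same shift to the follow-ups.

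**Working it through.** **The plan's own benchmark.** The planned effect is d = 0.6, entered as f = 0.3. A three-arm one-way F test with f = 0.3, alpha 0.05 and power 0.80 needs N = 111 (power 0.803), as stated, and 111 × 1.15 = 127.65 gives the stated 128. The point does not depend on these figures; d = 0.6 serves only as a yardstick.

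**Step 1: what the text implies.** Post-treatment visit = end of treatment; follow-ups = that date plus 6 and 12 months; cost end-date = that date plus 12 months. With TAU ending at GP-judged recovery, all four dates in TAU are functions of recovery. The TAU section describes one other exit, exclusion if the GP recommends psychological treatment. A patient who neither recovers nor is referred has none of the four dates.

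**Step 2: horizon.** Let D be treatment length in weeks and take 12 months as 52 weeks. The last visit falls at D + 52 weeks from the start of treatment. For group tCBT (D = 12–16, stated) this is weeks 64–68. TAU lengths are not given, so the values below are assumptions, as is a constant utility of 0.8 accrued from the start of treatment to the last visit. The QALY difference against a 12-week arm from window length alone is 0.8 × (D − 12)/52.

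| Assumed TAU length (weeks) | Last visit (week) | QALY difference from window length alone |
|---|---|---|
| 4 | 56 | −0.12 |
| 8 | 60 | −0.06 |
| 26 | 78 | +0.22 |
| 52 | 104 | +0.62 |

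No difference in health is involved. The cost window stretches or shrinks by the same number of weeks.

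**Step 3: symptom contrast with no true effect.** All inputs are assumptions: start mean 14, between- and within-person SD 3, entry at a score of 10 or more, monthly scores with autocorrelation ρ, mean decline of 0.5 or 1.0 points per month up to month 4. The GP ends TAU when the judged score is below 10, and patients not recovered are measured at month 12. The comparator is the same population measured at month 4. Bias = (mean at month 4 − mean at the TAU visit) / SD at month 4; positive values favour TAU.

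| ρ, decline per month | GP judges the exact score | GP error SD 3 | GP error SD 5 |
|---|---|---|---|
| 0.5, 0.5 | 0.47 | 0.30 | 0.14 |
| 0.5, 1.0 | 0.34 | 0.10 | −0.09 |
| 0.8, 0.5 | 0.27 | 0.16 | 0.02 |
| 0.8, 1.0 | 0.16 | −0.05 | −0.21 |

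The closer GP judgement tracks the questionnaire score, the more the timing favours TAU. When judgement is loose, TAU can close early and the sign can turn.

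**Step 4: how many patients lack an anchor.** A second model (baseline mean 14, mean decline 0.15 points per week, GP visit every 4 weeks, recovery cut at 10, 8 or 5) leaves 12% to 39% of TAU patients without a recovery date by week 52. This too is illustrative.

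**Step 5: can adjustment cure it?** TAU duration arises after randomisation and is itself a result of recovery. Conditioning on it compares tCBT patients with TAU patients sorted by outcome, so a duration covariate does not restore the randomised comparison. A mixed model that tolerates missing values does not help either if the visit is absent because the patient has not recovered.

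**The case against.** - **The trigger is inferred.** No sentence says that the GP's verdict triggers the TAU assessment; this follows from reading the TAU section together with Collection process. The latter refers to Table 2, which is not shown, nor is Fig. 1. Calendar weeks for TAU there would turn the point into a conflict of wording. This stands and lowers confidence, although the sections would still need reconciling.
- **It could be detail for the full protocol.** Visit windows often are. But the anchor and the TAU end rule are both stated here, and together they give a schedule that fails for some patients. That is more than an omission.
- **Outcomes are not GP judgements.** They are self-reported questionnaires, and assessors are to be blinded. This stands, and it is why the simulated bias shrinks or reverses once GP error is added.
- **Costs can be repaired in part.** Medical records are a source, so a common window from inclusion could be extracted for every arm. QALYs could be cut to a common horizon where visits cover it. Both are possible, but neither is stated in the article.
- **A stronger reading is tempting.** A reader might infer that TAU will look 0.56–1.06 SD better and that Hypothesis 2 is diluted or reversed. Those figures arise only if recovered TAU patients alone are measured and then compared with all patients at month 4. The same recovered patients at month 4 give about 0.2–0.7 SD, so part of the gap is selection, not timing. Measuring only recovered patients also sits badly with the planned intention-to-treat analysis, the telephone retention and the invitation of dropouts to the post-treatment assessment. The documents do not establish that size or direction.
- **GP blinding is a separate matter.** Whether asking patients not to disclose allocation supports the statement that "this will ensure that the GPs are blinded" is not needed for the timing point.

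**Conclusion.** The point holds on the visible text. Followed as written, TAU assessment dates depend on recovery, non-recovering TAU patients have no defined post-treatment visit, follow-up dates or cost end-date, and costs and QALYs run over different lengths of time by arm. The acknowledgements under Anticipated limitations set no rule.

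The horizon problem is the firmer part: under the assumed TAU lengths of 4–52 weeks and a utility of 0.8, window length alone moves accrued QALYs by −0.12 to +0.62 against a 12-week arm. The bias in the symptom contrast is uncertain in both size and direction, at about −0.2 to +0.5 SD in favour of TAU when all patients are measured. It depends mainly on how closely GP judgement follows the score. Its upper end is not small beside the planned 0.6. Confidence is moderate, because Table 2 and Fig. 1 could not be read.

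**What to change.** 1. Schedule assessments in all arms at common times from randomisation, whether or not treatment has ended. One example is week 16, the upper end of the stated group programme, then 6 and 12 months after that date.
2. Use one common window from randomisation for costs and QALYs in every arm, filling costs from medical records where needed.
3. Enter actual assessment time in the linear mixed model.
4. Reconcile the TAU, Collection process and Cost analysis sections with each other and with Table 2 and Fig. 1. When TAU care itself ends is a clinical matter and need not change.

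**Cost.** Wording and visit scheduling; the sample size is unaffected. Some tCBT participants would be assessed some weeks after, or just before, their last session. The project started in September 2021, so anyone already assessed under the present schedule would leave two timing schemes in one dataset. Those records need modelling by actual time, and where no assessment was made at a common time it cannot be recovered afterwards.

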### Therapist training

All the therapists are experienced clinical psychologists who work in the national health system. They study for 4–5 years to obtain a university degree and undergo a residency programme of 4 years to obtain clinical certification. They also undergo standardized training conducted by a supervisor PhD, when they learn the transdiagnostic therapy protocol. The course consists of studying a therapy handbook, four online lessons, and a face-to-face session with the trainer. All therapists will be supervised by a coordinator with whom they will be able to arrange follow-up sessions when they can resolve any doubts they may have during the intervention period.

### Outcomes

Primary outcomes are the screening of an ED and its severity. Secondary outcomes are the screening of other non-emotional mental disorders, symptom-related disability level, quality of life (general and health-related), the patient’s treatment satisfaction, and certain cognitive factors that have been observed to be common across different mental disorders [28–30]. Changes over time in all variables will be analysed (from pre-treatment to post-treatment and follow-ups) to assess treatment effectiveness. In addition, sociodemographic and medical data will be collected. Medical data will be used to calculate health care costs for cost-effectiveness analyses. Finally, health-related quality of life will be used to calculate the quality-adjusted life years (QALYs) for cost-utility analyses.

### Timeline

Table 2 shows the timeline as recommended in the SPIRIT statement [42].

**Table 2 Tab2:**
[figure not shown]
Study timeline according to SPIRIT Statement [42]

*CDTE* Questionnaire of Cognitive Distortions in Emotional Disorders, *CERQ* Cognitive Emotion Regulation Questionnaire, *CIDI* Composite International Diagnostic Interview, *EQ-5D-5L* 5-dimension, 5-level European Quality of Life scale, *GAD* Generalized Anxiety Disorder, *IACTA-PB* Inventory of Cognitive Activity in Anxiety Disorders-Panic Brief subscale, *MCQ-NB* Metacognitions Questionnaire-Negative Beliefs subscale, *PHQ* Patient Health Questionnaire, *PSWQ-A* Penn State Worry Questionnaire-Abbreviated, *RRS-B* Ruminative Responses Scale-Brooding subscale, *SCID-I* Structured Clinical Interview for DSM Axis-I Disorders, *SDS* Sheehan Disability Scale, *TAU* Treatment as usual, *tCBT* Transdiagnostic cognitive-behavioural therapy, *WHOQOL-BREF* WHO Quality of Life scale-Brief version

### Sample size

We used effect sizes from the previous literature to determine the sample size. Corpas et al.’s primary care RCT [41] compared both group and individual brief tCBT with TAU for emotional disorders and found low to medium effect sizes for all outcomes. Individual effects were larger (Cohen’s *d* ranged from .54 to .74) than group effects (.4 to .63) when compared with TAU; however, there was no significant difference between both transdiagnostic formats, with (very) low effect sizes (.06 to .27). Another primary RCT by Corpas et al. [36] compared tCBT with TAU and found medium to large effect sizes (from .39 for depression to .81 for panic symptoms). Finally, the PsicAP study compared the group tCBT used herein to TAU in primary care. Intention-to-treat analyses showed low to medium effect sizes over time for depression (Morris’ *d* ranged from .36 to .58), anxiety (.38 to .65), and somatizations (.31 to .4). Subsequently, we decided to assume a medium effect size of .6 (Cohen’s *d*).

Since software to determine sample sizes for linear mixed model analyses was not available, we used the *f* index of G*Power [52]. We assumed an effect size of .3 (the equivalent *f* value); a statistical power (1 - *β*) of .8; and a significance level (*α*) of .05, obtaining a required sample size of 111. However, to control withdrawals and take into account the abandonment rates in other similar trials [36, 41], we assumed a dropout rate of 15%, which brought the required sample size to 128.

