##### Somatization

The 15-item PHQ subscale (PHQ-15) [63] is the somatization module of the PHQ. It scores symptoms present in the previous 4 weeks from 0 *(not bothered at all*) to 2 (*bothered a lot*). It includes 13 somatic symptoms plus 2 from the PHQ-9 (sleeping problems and fatigue); cut points 5, 10, and 15 represent low, medium, and high somatic symptom severity, respectively. However, whereas the original algorithm requires a score of at least 2 in 3 or more somatic symptoms to screen a somatization disorder (a sensitivity of 78% and a specificity of 71%) [64], the cut-off point usually used is 10, as it is in the PHQ-9 and the GAD-7 [65]; nevertheless, since this number can be obtained with 10 symptoms rated with the minimum severity, we decided to join both criteria. Furthermore, although an absence of biological cause is also often required (since PHQ-15 does not distinguish between medically explained and unexplained symptoms) [63], the self-administered nature of the PHQ-15 makes it difficult for the subject to determine this. This tool has been validated with Spanish psychiatric outpatients (*α* = .78) [66].

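### The single 80% power at d = .6 does not hold for group tCBT versus TAU on PHQ-15: at the effects the protocol cites for this same therapy, power is about 26–40%

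*Protocol article*

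**What the plan says.** The Sample size section derives the planning effect from three earlier primary care trials and quotes these effects against TAU:

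- A three-arm trial, all outcomes together: individual format .54 to .74, group format .4 to .63.
- A second tCBT trial: from .39 (depression) to .81 (panic).
- The PsicAP study, which used the same group therapy: "Finally, the PsicAP study compared the group tCBT used herein to TAU in primary care". Its intention-to-treat effects, given as Morris' d, are .36 to .58 for depression, and for the other two scales "anxiety (.38 to .65), and somatizations (.31 to .4".

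The section then fixes one value: "Subsequently, we decided to assume a medium effect size of .6" (Cohen's d). It converts this for G*Power: "We assumed an effect size of .3 (the equivalent *f* value". With "a statistical power (1 - *β*) of .8" and "a significance level (*α*) of .05", the result is given as "obtaining a required sample size of 111", raised to 128 for 15% dropout. No endpoint or contrast is named.

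Four scales stand under Primary outcomes in the Data collection section: PHQ-9, GAD-7, PHQ-PD and PHQ-15. On the last: "The 15-item PHQ subscale (PHQ-15) [63] is the somatization module of the PHQ". The Analysis of clinical effectiveness section ties therapeutic success to means significantly lower than those of the controls, above all on the emotional disorder scores.

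**The concern.** A power statement without an endpoint will be read as applying to every primary scale. For the therapy actually under test, the protocol's own endpoint-level figures put .6 above the whole somatization range, just above the top of the depression range, and near the top of the anxiety range. Success is judged by significance against TAU, which is a pairwise question, whereas the calculation is for a three-group overall test.

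If the somatization effect is what the cited study found, the trial will more often than not miss it in group versus TAU. A reader who trusts the 80% could then take a non-significant PHQ-15 result as evidence of no benefit.

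**Working it through.** **Inputs from the protocol:** three arms, 1:1:1; alpha .05; power .8; d = .6; f = .3; N = 111, so 37 per arm; cited effects as above. **Assumptions:** pairwise tests are two-sided (sidedness is not stated), and Morris' d is entered as if it were Cohen's d, because the document gives nothing from which to convert it.

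**1. Reproduce 111.** One-way three-group F test, noncentrality λ = N f². With f = .6/2 = .3, λ = 111 × .09 = 9.99 on 2 and 108 df, and power is .803. The smallest balanced N that reaches .80 is 111. The protocol's figure reproduces.

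**2. Check the conversion from d to f.** f = d/2 holds for two groups. For three equal arms whose means span d, f is largest when two arms coincide at one end, for example means 0, d, d:

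f = √[((2d/3)² + (d/3)² + (d/3)²)/3] = d√2/3 = .471d.

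At d = .6, f = .283, λ = 111 × .08 = 8.88, and power is .75. This is also the pattern that Hypotheses 1 and 2 expect (two similar therapies, both better than TAU).

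**3. Pairwise power, group tCBT versus TAU.** Two-sample t test, 37 per arm, 72 df, noncentrality d√(37/2) = 4.301d.

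| Scale | Cited d, same group therapy | Power |
|---|---|---|
| PHQ-15 | .31 to .40 | .26 to .40 |
| PHQ-9 | .36 to .58 | .33 to .69 |
| GAD-7 | .38 to .65 | .36 to .79 |
| Planning value | .60 | .72 |

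No effect of this therapy on panic symptoms is cited, so PHQ-PD has no row. The smallest d with 80% pairwise power at 37 per arm is .66.

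**4. Is PHQ-15 rescued by other means?**

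- All 128 analysed (128/3 = 42.7, so about 42 per arm): .29 to .44.
- Baseline adjustment, with d divided by √(1 − ρ²), where ρ is an assumed baseline correlation: ρ = .3 gives .28 to .43; ρ = .5 gives .33 to .50; ρ = .7 gives .45 to .66.

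All stay below .80. Without adjustment, 80% pairwise power needs 100 per arm at d = .40 and 165 per arm at d = .31.

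**5. Could the individual arm lift the overall test?** With means 0 (TAU), .40 (group) and .54 (individual), f = .229 and omnibus power is .56. With individual at .74, f = .302 and power is .81. Group versus TAU stays at .40 in both cases.

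**The case against.** The strongest reply is that .6 was openly chosen as an assumption and is not foreign to the evidence. It lies inside four cited ranges: the three-arm trial's group (.4 to .63) and individual (.54 to .74) formats, the second trial (.39 to .81), and PsicAP anxiety (.38 to .65). The depression range misses it by only .02 at the top. The three-arm trial's ranges are not split by endpoint, so a somatization effect above .4 there cannot be excluded. A large individual-format effect could bring the omnibus test to about 80%. The PsicAP values are Morris' d over time, so a direct comparison with Cohen's d is approximate. All of this stands, and it limits the claim.

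A reader might infer that .6 has no support in the cited literature, or that 80% power fails for every primary scale and every test. The documents do not support either. With baseline adjustment at an assumed ρ of .5, pairwise power at d = .6 is .84, and at the top depression value (.58) it is .81. Nor does any section say that a null PHQ-15 result would be reported as no benefit; that is a risk of interpretation, not a stated plan.

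What the reply does not answer is the contrast for which the protocol has direct evidence: this group therapy against TAU on somatization. No somatization value above .4 appears in the document, and nothing in the individual arm changes that comparison.

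**Conclusion.** The point holds in a limited form. The arithmetic from f = .3 to 111 is right. What fails is the unqualified 80%.

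- **Firm:** for group tCBT versus TAU on PHQ-15, power at the cited effects is about 26–40% with 37 per arm, and no more than about 66% even with an assumed baseline correlation of .7.
- **Weaker:** PHQ-9 (33–69%) and GAD-7 (36–79%) fall short without adjustment, clearly at the low ends of their ranges and only modestly at the top.
- **General:** at d = .6 itself, unadjusted power is about 72% pairwise and at most about 75% for the three-arm test with means spanning .6, so the stated 80% rests on a two-group conversion.

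These figures assume two-sided alpha .05, 111 analysable participants, and Morris' d taken as approximately Cohen's d. A reader might go further and conclude that PHQ-15 should lose its primary status; low power for one contrast on one scale does not justify that.

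**What to change.** Keep N and revise the Sample size section:

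1. Say that d = .6 is an optimistic planning value and not a summary of the cited results for this therapy.
2. Replace the single 80% with therapy-versus-TAU power for each primary scale at the cited effects, computed pairwise and not through f = d/2. For group versus TAU without adjustment these are about 26–40% (PHQ-15), 33–69% (PHQ-9) and 36–79% (GAD-7). For PHQ-PD, say that no effect of this therapy is cited.
3. Note that the PsicAP values are Morris' d, and name any baseline correlation assumed if adjusted power is given.
4. State that a non-significant group-versus-TAU contrast on PHQ-15 will be reported with its confidence interval as inconclusive.

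PHQ-15 stays a primary outcome. The cost is wording only, with no extra participants; the stated power becomes less favourable.
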